### Randomization and Blinding

Allocation occurs in a 1:1 ratio to the treatment group (receiving metabolic resuscitation vs. standard shock management). We will use a permuted block randomization with variable block sizes of two, four and six stratified by site. Sealed opaque envelopes will be provided using a randomization sequence generated by The University of Queensland, Brisbane, Australia. Once a child meets eligibility criteria, study staff or treating clinicians are advised to open the next sequential sealed envelope to reveal the allocation of the patient.

Due to the challenges in blinding three drugs, and considering the main aim of this study to investigate feasibility of metabolic resuscitation, the study will be open label.

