### Statistical Analysis Plan

#### Sample Size

We define feasibility of recruitment if ≥65% of eligible patients are enrolled. Enrolment of 60 of 80 eligible patients will yield a recruitment rate of 75% with a one-sided lower 95% confidence interval limit of 66%, which would meet our feasibility metric for recruitment rate. We anticipate a recruitment period of 24 months to meet the target sample size of 60 participants; this sample should provide sufficient data on feasibility and safety, and indicate estimates of potential effect size to calculate power for a future full trial.

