#### Analysis

Using the Consolidated Standards of Reporting Trials (CONSORT) flow chart (Figure 1) (44) we will report on screened, included, and excluded patients, the number consented, and number of those with consent withdrawn. We will report on the number and proportion of children enrolled through prospective consent in comparison to consent to continue, timing of consent, and investigate the investigator-stated reasons if consent to continue was employed. Descriptive statistics will be used to compare demographics, clinical history and baseline clinical characteristics between the study arms (Supplementary Table 1), however statistical comparisons will not be undertaken. The estimate of the difference between the two study groups and the corresponding 95% confidence interval (CI) will be reported for outcomes relating to feasibility and clinical characteristics (Supplementary Tables 2 and 3). Quantile regression will be used to assess the comparison for continuous outcomes and the test of two proportions for binary outcomes. All analyses will be based on the intention-to-treat principle. All patients who underwent randomization and for whom consent is available are included in the ITT analysis. Protocol violations and major adverse events will be listed separately (Supplementary Table 4). A sensitivity analysis will be undertaken for primary and secondary outcomes, separating the standard care arm into two groups–those not receiving hydrocortisone, and those receiving hydrocortisone. Descriptive statistics only will be presented on the sensitivity analysis (Supplementary Table 5). In addition, we will provide graphs to describe temporal changes in pSOFA, physiological measures (heart rate, systolic blood pressure), serum lactate levels, use of fluid bolus volume (in ml/kg), and Vasopressor-Inotrope-Score (45) comparing the intervention group vs. controls, starting at time of randomization. Given the study sample, and that no stratification is performed, we will not perform other pre-planned subgroup analyses.

We anticipate that <30% of RESPOND PICU study patients will be co-enrolled into a concomitant study investigating early inotropes in sepsis, named RESPOND ED (ACTRN12619000828123). Analyses on RESPOND PICU will not be adjusted for co-enrolment in RESPOND ED given that both are pilot feasibility studies.

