### Current Trial Status

RESPOND PICU commenced recruiting in June 2019 with a projected completion date of June 2021. Recruitment is live at the central study site Queensland Children's Hospital, at Gold Coast University Hospital, and started recently at Sydney Children‘s Hospital, Westmead Children‘s Hospital, Perth Children‘s Hospital, Australia, and Starship Children‘s Hospital, New Zealand.

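### Analysis section denies the site stratification used at randomisation, and the planned between-arm comparisons name neither site nor baseline severity

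*Protocol article*

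**What the plan says.** Randomization and Blinding: "Allocation occurs in a 1:1 ratio to the treatment group", and "We will use a permuted block randomization with variable block sizes of two, four and six stratified by site". Current Trial Status lists six recruiting hospitals, so there are six strata.

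Analysis, on stratification: "Given the study sample, and that no stratification is performed, we will not perform other pre-planned subgroup analyses".

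Analysis, on methods: "Quantile regression will be used to assess the comparison for continuous outcomes and the test of two proportions for binary outcomes". On reporting: "The estimate of the difference between the two study groups and the corresponding 95% confidence interval (CI) will be reported". No covariate or stratum is named for any comparison. The only sentence about adjustment concerns the companion trial: "Analyses on RESPOND PICU will not be adjusted for co-enrolment in RESPOND ED".

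Data Collection provides for severity features at baseline, physiology and organ support at randomisation, and daily organ-dysfunction components from which pSOFA is calculated. Analysis plans pSOFA graphs that start at randomisation. A baseline pSOFA should therefore be available.

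The Introduction says that the article includes the statistical analysis plan, so the methods it names can be judged as stated.

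**The concern.** There are two linked but separate problems.

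The first is factual. One section stratifies allocation by site. Another denies any stratification and uses the denial to justify an analysis decision. A reader cannot tell from the Analysis section how the trial was randomised.

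The second is about precision. Site is plausibly prognostic on the article's own description. Control treatment follows institutional protocols, inotrope choice is left open, and other care follows local practice. The primary clinical outcome also assumes no organ dysfunction after PICU discharge for most survivors, so local discharge practice feeds into it. Severity at randomisation is an obvious candidate predictor of organ-dysfunction-free days. With about 30 children per arm, a chance imbalance in severity can move an unadjusted difference noticeably in any one realised trial.

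The Sample Size section wants effect-size estimates from this pilot to plan the power of a later trial, so the width of these intervals matters for a stated purpose.

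**Working it through.** **The plan's own figure.** The only computed figure in the Sample Size section is the one-sided lower 95% limit of 66% for 60/80. Wilson's formula with z = 1.645 gives (0.75 + 0.0169 − 1.645 × √(0.75 × 0.25/80 + 0.000106)) / 1.0338 = 0.663. Clopper-Pearson gives 0.658. The figure reproduces, and it does not depend on stratification or adjustment.

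**Inputs from the article.** N = 60 ("We anticipate a recruitment period of 24 months to meet the target sample size of 60 participants"), 1:1 allocation, six sites (five site terms), 95% intervals.

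**Assumed inputs.** R², the share of outcome variance explained by the added terms. The article gives nothing from which to derive it.

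**Formula.** Width ratio, adjusted to unadjusted = √(1 − R²) × t(0.975, 58 − q) / t(0.975, 58), where q is the number of added terms. This assumes that the arms are balanced on the covariates. Multiplying by √(57/(57 − q)) allows for chance imbalance.

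Example, site with R² = 0.05 and q = 5: √0.95 = 0.975, the t ratio is 1.002, and the imbalance factor is √(57/52) = 1.047. The ratio is 0.977 if balanced and 1.023 with chance imbalance.

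| Assumed R² | Site, balanced | Site, chance imbalance | Severity, chance imbalance | Site + severity, chance imbalance |
|---|---|---|---|---|
| 0 | 1.00 | 1.05 | 1.01 | 1.06 |
| 0.05 | 0.98 | 1.02 | 0.98 | 1.03 |
| 0.10 | 0.95 | 1.00 | 0.96 | 1.01 |
| 0.20 | 0.90 | 0.94 | 0.90 | 0.95 |
| 0.30 | 0.84 | 0.88 | 0.84 | 0.89 |

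Stratified blocks put site somewhere between its two columns. Over R² 0.05 to 0.20, site alone therefore runs from 2% wider to 10% narrower. Severity over R² 0.10 to 0.30 (correlations of √0.10 = 0.32 to √0.30 = 0.55) narrows intervals by 4 to 16%. In patient numbers that is about 1/0.957² = 1.09 to 1/0.844² = 1.40 times the sample.

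**Does this carry over to median regression?** A simulation used a 0 to 27 day outcome with deaths set to zero, site-stratified blocks of 2, 4 and 6, and 600 replicates per scenario. Its assumptions were one site with 40% of patients and five with 12% each, a residual SD of 6 days, severity slopes of 0, 3 or 6 days per SD, site SDs of 0, 2 or 4 days, and mortality of about 8% at average severity. Ratios of the SD of the adjusted to the unadjusted estimate were:

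- severity only: 0.61 to 1.03
- site only: 0.84 to 1.02
- both: 0.61 to 1.04

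With no site effect, a slope of 3 days (latent R² = 9/(9 + 36) = 0.20) gave 0.84 for severity, against 0.90 from the formula. An SD from 600 replicates has a relative standard error of roughly 1/√1200 = 3%, so differences of a few per cent are noise. The pattern agrees with the table: a clear gain if severity is prognostic, and little or a small loss if nothing is.

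**The case against.** The strongest reply is that only the wording is wrong. The sentence about stratification explains why no further subgroup analyses are planned. It may mean that there is no stratification by clinical factors, and it says nothing about covariates. A reader might infer that the authors leave the comparisons unadjusted because they believe there was no stratification. The documents do not support that link, and the two problems stand separately. The wording still has to be corrected, because as written it contradicts the randomisation section.

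A second reply is that quantile regression can carry covariates and that the article condenses a fuller protocol. This stands in part. For continuous outcomes, non-adjustment is inferred from silence. For binary outcomes it is not, because the named test is unadjusted.

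A reader might also infer that the intervals are certainly too wide, or that the estimates are biased. Neither follows. Randomisation keeps the crude difference valid, and ignoring strata is at worst conservative. No figure in the article shows that site or severity predicts outcome. For site alone the gain may be nil: at R² = 0.10 with chance imbalance the ratio is 1.00.

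The remedy also has limits. Covariates change the target from a difference in marginal medians to a conditional one. At the roughly 17% mortality cited in the Introduction, 60 × 0.17 ≈ 10 deaths would fall across 12 site-by-arm cells, and four of the six sites had only recently opened. These points argue for a pooling rule and for keeping the crude results. They do not argue for leaving the choice unstated.

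Finally, feasibility is the main aim, and its sample-size argument is untouched. That limits the importance of the point.

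**Conclusion.** The contradiction on stratification is plain and must be reconciled. The lack of any named adjustment is a moderate, conditional weakness in precision. It is explicit for binary outcomes and inferred for continuous ones, and it is not a source of bias.

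Most of the likely gain comes from severity, which is not a stratification factor. It is about 4 to 16% narrower intervals if severity explains 10 to 30% of outcome variance. Site alone ranges from about 2% wider to 10% narrower at R² of 0.05 to 0.20. If neither factor is prognostic, adjusting for both could widen intervals by up to about 6%.

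All these sizes rest on assumed R² values and a linear-model approximation. The median-regression simulation supports the direction but not an exact figure. No size was calculated for the binary outcomes.

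**What to change.** 1. Correct the Analysis section to say that allocation was stratified by site only. If the absence of clinical strata is a reason for limiting subgroup analyses, say that.
2. Pre-specify baseline pSOFA as a covariate in the quantile regression, together with site, and pool small sites by a rule fixed before the data are examined.
3. For binary outcomes, report a site-stratified Mantel-Haenszel risk difference with its 95% interval, using the same pooled sites.
4. Keep the crude differences as supporting results, and state that the adjusted median difference is conditional on the covariates.

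The cost is a few sentences and a few lines of code, with no new data collection. The price in analysis is the conditional interpretation and the possible widening of up to about 6% noted above.

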### Current Trial Status

RESPOND PICU commenced recruiting in June 2019 with a projected completion date of June 2021. Recruitment is live at the central study site Queensland Children's Hospital, at Gold Coast University Hospital, and started recently at Sydney Children‘s Hospital, Westmead Children‘s Hospital, Perth Children‘s Hospital, Australia, and Starship Children‘s Hospital, New Zealand.

### Significance

This worldwide first trial on metabolic resuscitation in paediatric sepsis will test the feasibility of an intervention showing promise of improving patient-centred outcomes and cost-effective health care delivery. Study sites include several paediatric hospitals across Australia and New Zealand, leveraging off of the ANZICS Paediatric Study Group network.

The study design is informed by the VITAMINS trial (24) and similar several recently published adult RCTs on metabolic resuscitation. While the optimal dosing of metabolic resuscitation, in particular of ascorbic acid, remains uncertain, weight-based dosing schedules were derived from adult studies, considering expert pediatric critical care pharmacist advice. Of note, we recently reviewed the literature on harm related to high dose ascorbic acid in children and identified that the safety of this intervention is very high even at doses superior to those used in this trial (46). Inclusion and exclusion criteria of this pilot study were adapted from adult trials towards pediatric populations, but it is acknowledged that criteria such as cardiomyopathy were not defined in detail to keep the study pragmatic. Limitations include lack of a dedicated hydrocortisone only arm, and hence pre-planned subgroup analyses on children treated with hydrocortisone, vs. controls without hydrocortisone, and vs. intervention with metabolic resuscitation, will be performed.

The interventions are low cost and are based on globally available drugs with excellent safety profiles_._ The study design is pragmatic, and findings will serve to inform the design of a fully powered trial on high dose ascorbic acid, thiamine, and hydrocortisone in children with septic shock.

## Ethics Statement

The studies involving human participants were reviewed and approved by Children's Health Queensland, Brisbane, HREC/18/QCHQ/49168. Written informed consent to participate in this study was provided by the participants' legal guardian/next of kin.

